**FIGURE 2 F2:**
[figure not shown]
The illustration of fNIRS data acquisition.

**FIGURE 3 F3:**
[figure not shown]
Blood oxygen parameters of cerebral cortex and upper limb flexors are synchronously detected during the grasping task.

Before the actual data collection, a practice session was conducted to familiarize participants with the tasks. The fNIRS data collection followed a block design paradigm. Each condition was preceded by 50 s of rest, which served as a baseline period to stabilize the fNIRS signal. Between each condition, participants were allowed a 2-min break. Each condition consisted of three blocks, with each block consisting of a 20-s motor task period followed by a 20-s rest period. During all rest periods, participants were instructed to keep their focus still on the handle of the ARAT toolbox.

#### fNIRS system and data analysis of cerebral cortex

In this study, the NirSmart-6000A equipment (Danyang Huichuang Medical equipment Co., Ltd, China) was used to continuously measure and record changes in the concentration of HbO and HbR in the cerebral cortex during the grasping task. The system consisted of near-infrared light sources (LEDs) and avalanche photodiodes (APDs) as detectors. The wavelengths used were 730 nm and 850 nm for the LED and APD, respectively, and the sampling rate was 11 Hz. Fourteen light sources and fourteen detectors were used, forming a total of 35 effective channels (CHs) as shown in Figure 4. The average distance between the light sources and detectors was 3 cm, ranging from 2.7 cm to 3.3 cm. To define the coordinates of the acquired channels, an NIRS-EEG compatible cap from EASYCAP, Herrsching, Germany, based on the international 10/20 system, was used for localization. The brain regions observed in this study were the bilateral prefrontal cortex (LPFC/RPFC), motor cortex (LMC/RMC), and occipital lobe (LOL/ROL), according to existing literature. No detector signal supersaturation occurred during the recording process. The middle point of each channel was defined as the main brain region detected by that channel, and the coordinates of each channel were calibrated using this point as the center of a circle. The Montreal Neurological Institute (MNI) coordinates of each channel were calculated and registered based on the 10-20 system using the NIRSpark (Danyang Huichuang Medical equipment Co., Ltd, China). The corresponding brain regions were then identified in the adult Brodmann Chris Rorden’s MRIcro brain model. The coordinates of each channel and the calibration information of the brain regions are provided in Table 1.

**FIGURE 4 F4:**
[figure not shown]
The arrangement of fNIRS channels of cerebral cortex.

**TABLE 1 T1:** The coordinates of each channel and the calibration information of brain region.

Channel	Sources	Detectors	X	Y	Z	Brodmann Area (Chris rorden’ MRIcro)	Percentage
CH1	S1	D1	52.356	−1.9313	55.131	6−Pre-Motor and Supplementary Motor Cortex	0.9012
CH2	S1	D6	56.299	−23.562	56.601	1−Primary Somatosensory Cortex 3−Primary Somatosensory Cortex	0.4436 0.428
CH3	S2	D2	55.399	41.65	1.9866	45−pars triangularis Broca’s area	0.6744
CH4	S2	D7	59.693	29.199	14.255	45−pars triangularis Broca’s area	0.9135
CH5	S3	D2	41.854	60.848	5.2035	10−Frontopolar area	0.659
CH6	S3	D3	19.831	71.754	8.2877	10−Frontopolar area	0.9521
CH7	S3	D8	29.242	63.37	19.568	10−Frontopolar area	0.7386
CH8	S4	D3	−10.758	73.07	10.168	10−Frontopolar area	1
CH9	S4	D4	−35.079	62.495	11.108	10−Frontopolar area	0.7358
CH10	S4	D9	−21.034	65.834	24.694	10−Frontopolar area	0.8321
CH11	S5	D4	−52.275	42.85	10.496	45−pars triangularis Broca’s area	0.7786
CH12	S5	D10	−56.346	28.713	24.181	45−pars triangularis Broca’s area	0.8309
CH13	S6	D5	−55.973	−23.32	57.463	3−Primary Somatosensory Cortex	0.5484
CH14	S6	D11	−45.237	−23.017	66.994	3−Primary Somatosensory Cortex 4−Primary Motor Cortex	0.4483 0.5211
CH15	S7	D1	42.319	−2.2922	62.568	6−Pre-Motor and Supplementary Motor Cortex	0.8943
CH16	S7	D6	45.142	−23.342	67.067	4−Primary Motor Cortex	0.5904
CH17	S7	D12	33.732	−24.261	73.163	4−Primary Motor Cortex	0.6545
CH18	S7	D13	30.879	−4.5054	68.988	6−Pre-Motor and Supplementary Motor Cortex	1
CH19	S8	D2	46.574	49.425	18.266	46−Dorsolateral prefrontal cortex	0.642
CH20	S8	D7	51.663	35.728	29.39	45−pars triangularis Broca’s area	0.9425
CH21	S8	D8	36.333	51.127	30.619	46−Dorsolateral prefrontal cortex	0.8843
CH22	S9	D3	6.9278	68.503	23.942	10−Frontopolar area	1
CH23	S9	D8	16.238	59.508	34.233	9−Dorsolateral prefrontal cortex	0.6039
CH24	S9	D9	−8.4826	60.969	37.456	9−Dorsolateral prefrontal cortex	0.6577
CH25	S10	D4	−42.728	50.755	24.327	46−Dorsolateral prefrontal cortex	0.6624
CH26	S10	D9	−29.041	53.06	37.191	9−Dorsolateral prefrontal cortex 46−Dorsolateral prefrontal cortex	0.4318 0.5682
CH27	S10	D10	−45.617	35.222	37.851	45−pars triangularis Broca’s area	0.4762
CH28	S11	D5	−50.878	−2.2923	56.073	6−Pre-Motor and Supplementary Motor Cortex	0.9298
CH29	S11	D11	−40.425	−0.87957	63.65	6−Pre-Motor and Supplementary Motor Cortex	0.977
CH30	S12	D12	20.744	−25.16	77.428	4−Primary Motor Cortex	0.6824
CH31	S12	D13	20.445	−2.6141	76.598	6−Pre-Motor and Supplementary Motor Cortex	1
CH32	S13	D11	−34.819	−22.105	73.515	4−Primary Motor Cortex	0.6528
CH33	S13	D14	−23.263	−20.709	77.36	4−Primary Motor Cortex 6−Pre-Motor and Supplementary Motor Cortex	0.4542 0.5458
CH34	S14	D11	−30.534	−1.1513	68.7	6−Pre-Motor and Supplementary Motor Cortex	1
CH35	S14	D14	−19.211	−0.49547	76.226	6−Pre-Motor and Supplementary Motor Cortex	1

Some channels may cover more than one brain region. To save space in this paper, only the brain regions with a coincidence degree higher than 0.4 are listed in this table.

For data analysis, the NirSpark software package, running in MATLAB (The Mathworks, USA), was utilized. The data preprocessing involved several steps, including eliminating irrelevant time intervals, removing non-related artifacts, converting light intensity to optical density, applying a band-pass filter, converting optical density to blood oxygen concentration, and setting parameters for the hemodynamic response function (HRF). The HRF initial time was set to −2 s, and the end time was set to 40 s, with a baseline state from −2 s to 0 s and a single block paradigm from 0 s to 40 s. Both the “start” and “rest” durations were set to 20 s. The blood oxygen concentration data from the three block paradigms were then averaged to generate a block average result. These preprocessing steps allowed for meaningful analysis of the fNIRS data, providing insights into changes in cerebral blood flow and oxygenation during the experimental conditions.

In this study, the Generalized Linear Model (GLM) (Uga et al., 2014) was utilized to analyze the pre-processed time-series data of HbO for each channel and subject. A t-test was performed (P < 0.05) to compare the baseline and task states. The GLM allowed for the establishment of an ideal Hemodynamic Response Function (HRF) specific to each task and subject. The similarity between the experimental and ideal HRF values was evaluated (Chung et al., 2018). The beta value, representing the level of cortical activation for each channel, was used as an estimate of the HRF prediction for the HbO signal (Kawabata et al., 2019). It indicates the peak value of the HRF function and serves as a measure of cortical activation.

Wavelet amplitude (WA) of hemoglobin signal calculated by wavelet transform was used to quantify the intensity of cortical activity. For a single channel, 3 time windows of 20 s were divided to calculate the average WA value in the frequency domain, that is, 3 cortical activity intensity indices could be obtained. The intensity of cortical activity in a cortical region was calculated as the average WA value for all channels in that region. The WA-based laterality metric was calculated by the following equation:

LateralizationIndex=(WAaffected-WAunaffected)/

(WA⁢affected+WA⁢unaffected).

where WA affected denotes the mean WA value in the cortical region of affected hemisphere and WA unaffected denotes the mean WA value in the homologous cortical region of the unaffected hemisphere. The value of WA laterality ranges from 1 to 1. Positive values imply that the affected side cortical activity is greater than the unaffected side, and negative values imply that the unaffected side is greater than the affected side.

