### fNIRS data acquisition and analysis

The fNIRS data acquisition process is illustrated in Figures 2, 3. The participants were seated comfortably in an adjustable chair within a quiet room. For participants in Group A, they were instructed to grasp a 2.5 cm^3^ wooden block first with their unaffected hand and then with their affected hand. Participants in Group B performed two sets of tests, grasping a 2.5 cm^3^ wooden block and a 5 cm^3^ wooden block, using their unaffected hand first and then their affected hand. Subjects in Group C were asked to sequentially pick up three blocks of different sizes, again using their unaffected hand first and then their affected hand. The control group was required to grasp and lift three different sizes of cubic wooden blocks, first with their right hand and then with their left hand.

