### Statistical analysis

Before conducting parametric tests, several steps were taken to prepare and analyze the data. Outliers were identified using normal Q–Q plots and box plots, and data points that were more than three standard deviations from the mean were considered outliers and subsequently excluded from the analysis (Minati et al., 2011). Missing values were addressed using multiple imputation analysis to estimate and replace the missing data points (Blankers et al., 2010).

Descriptive statistics were used to summarize the demographic and clinical characteristics of the study participants. The normality of the data distribution was assessed using the one-sample Kolmogorov-Smirnov test. For comparisons between different groups, chi-square tests were used for categorical variables, while independent t-tests were used for continuous variables.

To evaluate the differences in outcome measures before and after the intervention for participants with stroke, paired sample *t*-tests were employed. The correlations between variables were assessed using either the Pearson correlation coefficient (r) or the Spearman correlation coefficient (ρ), depending on the nature of the data.

The significance of interregional coupling strength between the resting state and different grasping states was evaluated using a one-way analysis of variance (ANOVA). Additionally, χ^2^ tests were utilized to identify statistically significant differences in interregional coupling direction between the resting state and different grasping states.

All statistical analyses were performed using SPSS software (version 20.0; SPSS Inc., Chicago, IL, USA). All tests were two-tailed, and a significance level of *p* < 0.05 was considered statistically significant.

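### Task response is tested in each of 35 cortical channels at an unadjusted P < 0.05, so 1.75 false channels are expected per grasp condition when none responds

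*Protocol article*

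**What the plan says.** The Protocol article, section on the fNIRS system and data analysis of cerebral cortex, describes the montage: "Fourteen light sources and fourteen detectors were used, forming a total of 35 effective channels (CHs) as shown in Figure 4". Table 1 lists CH1 to CH35, which agrees.

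The same section says that a GLM "was utilized to analyze the pre-processed time-series data of HbO for each channel and subject", and then: "A t-test was performed (P < 0.05) to compare the baseline and task states". It reads the result channel by channel: "The beta value, representing the level of cortical activation for each channel, was used as an estimate of the HRF prediction for the HbO signal".

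The Statistical analysis section closes with a general rule: "All tests were two-tailed, and a significance level of" p < 0.05. Nothing in the article mentions an adjustment across channels or conditions.

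The section on fNIRS data acquisition fixes the number of conditions per session. For Group A, "they were instructed to grasp a 2.5 cm^3^ wooden block first with their unaffected hand and then with their affected hand", which is two conditions. Group B uses two block sizes with each hand (four). Group C and the healthy controls use three block sizes with each hand (six).

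The primary objective, at the end of the Introduction, includes analysing how strongly functional areas of the cortex are activated.

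**The concern.** A test of task against baseline, repeated in 35 channels at 0.05 each, is the usual basis for saying which parts of the cortex respond to a task. Used that way without adjustment, some channels will pass by chance in every condition where the true response is absent or confined to a few channels. The article could then report a cortical site as engaged at a given grasp level on noise alone.

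The issue sits inside one condition and one signal. Naming a single lead outcome elsewhere in the plan would not change which of the 35 channels pass this test.

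**Working it through.** The article gives no familywise error rate or calculated sample size for this analysis, so there is no stated figure to reproduce. Its per-test level is taken as given.

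**Inputs**
- Channels: m = 35 (cortical fNIRS section; Table 1).
- Level per test: 0.05, two-sided (same section; Statistical analysis).
- Conditions per session: A 2, B 4, C and controls 6 (data acquisition section).
- Group size for a group-level version of the test: n = 20 (Participants, Sample Size).
- Correlation between channel statistics: **not given; assumed**, range 0 to 0.9.
- Each test is assumed to hold its nominal 5% level, and no channel truly responds.

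**1. Expected false channels per condition.** m x 0.05 = 35 x 0.05 = 1.75. An expected count adds over channels whatever their dependence, so no correlation assumption is needed.

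**2. Chance of at least one, independent channels.** 1 - 0.95^35 = 0.834, or 83%. The chance of two or more is 52.8% (binomial, 35 trials at 0.05).

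**3. Chance of at least one, correlated channels (simulated).** Equal correlation between all pairs, two-sided tests at 0.05; 100,000 draws for the normal statistic and 20,000 for the one-sample t-test with n = 20:

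| Assumed correlation | Normal statistic | t-test, n = 20 |
|---|---|---|
| 0 | 83% | 83% |
| 0.3 | 71% | 72% |
| 0.5 | 54% | 56% |
| 0.6 | 45% | not run |
| 0.7 | 36% | 38% |
| 0.9 | 18% | not run |

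The two columns agree to within about two points; rounded between them, the figures are about 72%, 55% and 37% at 0.3, 0.5 and 0.7. A separate run let correlation decay with distance between the Table 1 coordinates. It gave 78%, 73%, 62% and 45% at average nearest-neighbour correlations of 0.46, 0.60, 0.73 and 0.86.

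**4. Per session.** Expected false channels, summed over conditions: A 2 x 1.75 = 3.5; B 4 x 1.75 = 7.0; C and controls 6 x 1.75 = 10.5.

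**5. After adjustment.** In a simulation with n = 20 and equal correlations of 0.2, 0.4 and 0.6, the chance of any false channel fell from 77.8%, 64.0% and 48.0% unadjusted to 4.8%, 4.1% and 4.2% with Benjamini-Hochberg at 5%. For comparison, Bonferroni would test each channel at 0.05/35 = 0.00143; with independent channels the chance of any false channel is then 4.9%.

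**The case against.** The strongest reply is that the article never states a decision rule. It does not say that a channel passing the test is declared active, and it draws no cortical activation map; the only map it names is for the muscle signal. The activation measure it does name, the beta, is continuous. This stands: the use of the test is an inference, and the point is conditional on that use. But the article gives the test no other evident purpose.

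A second reply is that a condensed article may leave channel correction to an analysis plan not shown here, and that a threshold of 0.05 does not exclude adjusted p-values. This stands in part. Silence alone would not be a finding. Here, however, the article states the numerical criterion for this test and repeats it for all tests, and followed as written that rule gives the error rates above.

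A reader might go further in three ways that the documents do not support.
- One might infer that false channels will usually appear in any single condition. That holds only up to an average correlation of about 0.5; at 0.6 the chance is already below half.
- One might infer that comparisons between Groups A, B, C and controls will be contaminated, the more so because 3.5, 7.0 and 10.5 rise with grasp function. The article plans no comparison of thresholded channel sets and no tally of channels over conditions.
- One might infer that the primary outcomes are compromised. The cortical measures under Primary outcomes (regional wavelet amplitude, the lateralization index, coupling strength) do not depend on this test. Regional amplitude averages all channels in a region, without thresholding.

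Two further limits stand. The probabilities describe the case in which no channel responds, a limiting case for a grasping task recorded over motor cortex. And the article does not settle whether the t-test is run per subject or per group; the n = 20 runs represent the group version.

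**Conclusion.** The concern holds in a limited form. Thirty-five channel tests at an unadjusted 0.05 give 1.75 expected false channels per condition when none responds. That figure needs only the stated level and tests that hold it. The 83% chance of at least one is the independence figure. The range of about 72% to 37% rests on assumed correlations of 0.3 to 0.7. The reach is confined to channel-level statements about activation, which is part of the primary objective. It is worth correcting because the remedy is cheap, but it does not threaten the named regional and connectivity outcomes.

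**What to change.** In the section on cortical fNIRS analysis, add that the 35 channel p-values within each condition are adjusted by Benjamini-Hochberg at 5%, that adjusted p-values are reported, and that a channel is described as responding only on its adjusted value.

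This is about one line of analysis code and needs no new data or patients. The price is that weakly responding single channels are declared less often. The guarantee should be worded with care. When no channel responds, the chance of any false channel is about 5%, given independent or positively dependent channels. When some do respond, the method controls the expected proportion of false channels among those declared, and not the chance of any. Because it works within a condition, it does not control error across the two to six conditions of a session, and the text should say so.

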### Participants

Inclusion Criteria:

1.First stroke confirmed by CT or MRI.2.Medically stable.3.Age between 40 and 80 years.4.Onset of stroke occurred between two weeks to three months.5.Right handedness.6.No severe cognitive impairment (MMSE ≥ 22 points) and able to follow motor commands.7.Able to maintain an upright position in an armless seat for at least 30 min.8.Modified Ashworth grade of the affected upper limb is equal to or less than grade 2.9.Brunnstrom motor function grade of the affected hand is equal to or greater than grade 3, and able to grasp a 2.5cm3 wood block with effort.10.Patient and their family members agree to participate in the study and have signed the informed consent.

Exclusion Criteria:

1.Unstable clinical condition.2.Presence of any neuropsychiatric illness other than stroke.3.Diagnosis of schizophrenia, bipolar disorder, obsessive-compulsive disorder, personality disorder, or major depression.4.Presence of skin lesions or infections on the upper limb.5.History of upper limb fractures, deformities, or finger absence.

Sample Size:

Based on the sample size of previous studies (Huo et al., 2019a), a total of 60 patients following stroke will be enrolled in this study, with 20 patients in each of the three groups.

Group A: Patients who can only grasp and lift a 2.5 cm^3^ wooden block with their hemiplegic hand.Group B: Patients who can grasp and lift 2.5 cm^3^ and 5 cm^3^ blocks with their hemiplegic hand but cannot lift 10 cm^3^ blocks.Group C: Patients who can pick up 2.5 cm^3^, 5 cm^3^, and 10 cm^3^ wood blocks with their hemiplegic hand but exhibit abnormalities in speed and coordination during the task.

In addition, a control group of 20 age-matched healthy subjects without neurological diseases or history of upper limb trauma will also be enrolled.

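### Prefrontal lateralization index: Table 1 shows a consistent left-right offset in channel position, and the between-group tests take no account of lesion side

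*Protocol article*

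**What the plan says.** Under the heading on the fNIRS system and data analysis of cerebral cortex, the protocol article names the regions as "bilateral prefrontal cortex (LPFC/RPFC), motor cortex (LMC/RMC), and occipital lobe (LOL/ROL"). A region's activity is "calculated as the average WA value for all channels in that region". The lateralization index is (WA affected − WA unaffected)/(WA affected + WA unaffected), where the second term is "the mean WA value in the homologous cortical region of the unaffected hemisphere". Primary outcomes lists the WA-based inter-hemispheric index as a measure of activation moving from the affected to the healthy side.

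Table 1 ("The coordinates of each channel and the calibration information of brain region") prints X, Y, Z and Brodmann overlap for each of the 35 channels. It has no column that assigns a channel to left or right prefrontal cortex.

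The inclusion criteria require "Right handedness" but do not restrict the side of the lesion. The stroke groups are formed by the block sizes a patient can lift, in a non-randomised design. Statistical analysis names independent t-tests for continuous variables in comparisons between groups, with no adjustment. For change over the intervention, "paired sample *t*-tests were employed".

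**The concern.** The index can be read as a hemispheric contrast only if the two regional averages sample corresponding tissue. If the left prefrontal optodes sit consistently higher and more medial than the right ones, part of any right-left difference in WA may come from position.

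Such a difference would not average out in a simple way. In a patient with a right-sided lesion the right hemisphere is the affected one, so a right-minus-left difference enters with a plus sign. In a patient with a left-sided lesion it enters with a minus sign. A group's mean index then depends on how many of its patients have lesions on each side. With groups formed by grasp ability and 20 patients in each, nothing makes that mix equal, and a difference in mix could be taken for a difference in activation transfer between levels of grasp function.

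**Working it through.** **Inputs.** The X, Y, Z coordinates of all 35 channels come from Table 1. Channels with Y > 20 mm were taken as prefrontal and the rest as motor or somatosensory. Side is the sign of X.

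**Channel count.** Prefrontal: 10 with X > 0 (CH3–7, 19–23) and 9 with X < 0 (CH8–12, 24–27). Motor: 8 and 8. The sum 10 + 9 + 8 + 8 = 35 agrees with the stated total.

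**The odd channel.** CH22 joins S9 and D3. D3 also serves CH6 (right) and CH8 (left), and S9 also serves CH23 (right) and CH24 (left). By layout CH22 is therefore the midline channel of a 9 + 9 array, although it is registered at X = +6.9 mm.

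**Pair offsets.** For each left channel X was replaced by |X|, and the right partner's coordinates were subtracted. Pairs were matched by optode layout, and an optimal distance assignment gave the same pairs. Values are in mm. Negative X means the left channel is nearer the midline, and positive Z means it is higher.

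| Right/left | X | Y | Z | Distance |
|---|---|---|---|---|
| CH3/11 | −3.1 | +1.2 | +8.5 | 9.1 |
| CH4/12 | −3.3 | −0.5 | +9.9 | 10.5 |
| CH5/9 | −6.8 | +1.6 | +5.9 | 9.1 |
| CH6/8 | −9.1 | +1.3 | +1.9 | 9.4 |
| CH7/10 | −8.2 | +2.5 | +5.1 | 10.0 |
| CH19/25 | −3.8 | +1.3 | +6.1 | 7.3 |
| CH20/27 | −6.0 | −0.5 | +8.5 | 10.4 |
| CH21/26 | −7.3 | +1.9 | +6.6 | 10.0 |
| CH23/24 | −7.8 | +1.5 | +3.2 | 8.5 |
| **Mean** | **−6.2** | **+1.2** | **+6.2** | **9.4** |

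All nine pairs shift medially and upward. The eight motor pairs give a mean shift of (−0.2, +1.7, +0.3) mm and a mean distance of 2.4 mm (range 0.3 to 5.1).

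**Regional averages.** With 10 right against 9 left channels, the mirrored centroids differ by (−2.9, −0.6, +5.6) mm, or √(2.9² + 0.6² + 5.6²) ≈ 6.3 mm. Without CH22 they differ by (−6.2, +1.2, +6.2) mm, or √(6.2² + 1.2² + 6.2²) ≈ 8.8 mm.

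**Effect on the index.** Suppose true activity is equal on both sides and position alone makes one side's mean WA (1 + g) times the other's. The index is then g/(2 + g) for lesions on one side and −g/(2 + g) for lesions on the other, a gap of 2g/(2 + g). The documents give no value for g, so these values are assumptions:

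| g | Shift | Gap between lesion sides |
|---|---|---|
| 1% | 0.005 | 0.010 |
| 5% | 0.024 | 0.049 |
| 10% | 0.048 | 0.095 |
| 20% | 0.091 | 0.182 |

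The false difference between two groups is that gap times the difference in their proportions of right-sided lesions. For illustration, 12 of 20 against 8 of 20 is a difference of 0.2. That gives 0.095 × 0.2 = 0.019 at g = 10% and 0.182 × 0.2 = 0.036 at g = 20%.

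**The case against.** **The offset may be an artefact of registration.** Table 1 is one set of coordinates, not a record of each patient's cap. Rotating all prefrontal channels about the origin by about 4.7° of roll and 1° of yaw cuts the mean pair distance from 9.4 to 2.5 mm, close to the motor figure, and brings CH22 to under 4 mm from the midline. This stands: the table cannot say whether the tilt was on the head or in the software.

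**The sides are still broadly homologous.** A reader might infer that the index does not compare homologous regions at all. Table 1 does not support that. Every pair shares a Brodmann label, and the offset is about a third of the optode spacing ("The average distance between the light sources and detectors was 3 cm"). A shared label is not equal sampling, however. CH20 overlaps area 45 by 0.94 and its partner CH27 by 0.48. CH21 overlaps area 46 by 0.88, while CH26 is split 0.57 and 0.43 between areas 46 and 9.

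**The 10 to 9 count is not a bias.** The regional value is a mean, so unequal numbers do no harm in themselves. Nor does the article say that CH22 is counted as right.

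**The size is unknown.** Nothing links a shift of 6 to 9 mm to a change in WA, and at 1% the index moves by only 0.005. No lesion-side distribution is given, so imbalance between Groups A–C is a possibility and not a fact.

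**Paired tests largely escape.** A fixed offset approximately cancels in the pre-post comparison if cap placement is reproduced. That does not help the cross-sectional comparison, which serves the primary objective.

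**Covariates are often left to the analysis plan.** That is fair in general. Here the article does name the between-group test, and it is an unadjusted one.

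**Conclusion.** The point holds as a conditional one. Two parts are established: the tabulated prefrontal coordinates are offset by about 6 mm medially and 6 mm in height (9.4 mm in 3-D), in the same direction in all nine pairs and far beyond the motor pairs; and a fixed right-left difference of any origin reverses sign in the index with lesion side. The named between-group tests do not handle that reversal.

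Three things remain unknown: whether the offset existed on patients' heads, how much it changes WA, and how lesion side is spread over Groups A–C. The figures of 0.01 to 0.18 rest on assumed amplitude differences of 1% to 20% and on an offset that is constant across patients. The documents do not support saying that the index is shown to be biased, that the groups are unbalanced, or that the left channels are 9 mm higher. The change is worth making because it costs little and protects a primary outcome.

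**What to change.** 1. Include lesion side as a covariate, or stratify by it, in every between-group comparison of the prefrontal lateralization index among Groups A–C. A linear model with group and lesion side replaces the independent t-test. The cost is one degree of freedom, and lesion side is already known from the CT or MRI used for eligibility. The lesion-side coefficient should not be read as a measure of the montage effect, since lesion side may also have a real effect in right-handed patients.
2. Check the prefrontal registration. If the coordinates are wrong, correct Table 1. If they are right, describe the two sides as approximately homologous.
3. Leave the midline channel CH22 out of both prefrontal averages, or state how it is handled. This settles a definition but does not remove the offset: the centroid gap is 6.3 mm with CH22 on the right and 8.8 mm without it.
4. Keep the cross-sectional comparison. Pre-post change should not replace it as the main laterality result, because that would displace the primary objective.

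Items 1 and 3 are changes of analysis wording. Item 2 needs one check of the existing registration.
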